#### Intervention

IY-T is the intervention. Parents living in the BSB area with a child aged 1–3 are eligible to enrol in IY-T. IY-T receive most of their enrolled participants through their own engagement with the community directly, and also through engaging with schools and nurseries. IY-T aim to recruit approximately 12 parents to each group that they run.

Within IY-T, parents learn how to help their toddlers feel loved and secure, encourage social and emotional development, and establish strategies for developing routines, handling separation, and managing misbehaviour [15]. Parents/carers receive 3 promotional contacts prior to the beginning of the group via assertive outreach, consisting of telephone contact and at least one home visit. The initial telephone contact introduces the parents to the project and Group Facilitators, and aims to build the participants confidence in attending. The home visits are intended to create a sense of rapport between the family and Group Facilitators and alleviate any barriers that families might have in accessing the group such as crèche, language difficulties, or concerns about what the group might involve. The intervention will be delivered in a combination of face-to-face and virtual formats (dependent on lockdown rules in place during the COVID-19 pandemic at the time of the study and participant needs) by trained Group Facilitators who receive regular supervision from an accredited IY mentor.

The 13 IY Toddler Basic sessions cover eight topics:

Part one –Child-Directed Play Promotes Positive RelationshipsPart two–Promoting Toddler’s Language with Child-Directed CoachingPart three–Social and Emotion CoachingPart four–The Art of Praise and EncouragementPart five–Spontaneous Incentives for ToddlersPart six–Handling Separations and ReunionsPart seven–Positive Discipline-Effective Limit SettingPart eight–Positive Discipline-Handling Misbehaviour

Further detail on the content and delivery of the IY-T intervention, and materials, can be found here: https://incredibleyears.com/programs/. The IY-T theory of change and logic model developed by Barnardo’s for Bradford delivery states that IY-T will result in improvements in child social and emotional development over the medium and long term. The logic model is provided in a S2 File.

### Outcome (early years foundation stage profiles)

The primary and secondary outcomes are obtained through the child’s Early Years Foundation Stage Profile Profile (EYFSP) which will be linked to individual BiBBS children through their routine education records. The EYFSP is completed by teachers for children when they reach age five, at the end of their last term in reception. It contains 17 Early Learning Goals (ELGs) relating to different areas of learning. Previously, children were assigned a score of either “Emerging” (not reaching expected levels), “Expected” (reaching expected levels), or “Exceeding” for each ELG [30, 31]. For the new EYFSP (post September 2021), children are assigned a score of either “Emerging” or “Expected” for each ELG. See Table 1 for an overview of both the new and old EYFS ELGs.

**Table 1 pone.0291557.t001:** Overview of the early learning goals (ELGs) in the old and new versions of the Early Years Foundation Stage Profile (EYFSP).

Area of Learning	“Old” EYFS ELGs (See Section 6 of 2021 EYFSP handbook for further detail)	“New” EYFS ELGs (See Section 3.4 of 2021 EYFSP early adopter handbook for further detail)
**Communication and language development (primary outcome)**	**1. Listening and attention** **2. Understanding** **3. Speaking**	**1. Listening, attention and understanding** **2. Speaking**
Physical development	4. Moving and handling 5. Health and self-care	3. Gross motor skills 4. Fine motor skills
**Personal, social and emotional development (primary outcome)**	**6. Self-confidence and self-awareness** **7. Managing feeling and behaviour** **8. Making relationships**	**5. Self-regulation** **6. Managing self** **7. Building relationships**
Literacy	9. Reading 10. Writing	8. Comprehension 9. Word reading 10. Writing
Mathematics	11. Numbers 12. Shape, space and measures	11. Number 12. Numerical patterns
Understanding the world	13. People and communities 14. The world 15. Technology	13. Past and present 14. People, culture and communities 15. The natural world
Expressive arts and design	16. Exploring and using media and materials 17. Being imaginative	16. Creating with materials 17. Being imaginative and expressive

Note: 1. For a detailed description of what is expected of a child within an ELG, see GOV.UK [2021] [32].

2. The bolded ELG’s are the goals used for the primary outcome.

The EYFSP is an important predictor of later academic attainment and developmental difficulties [33, 34]. Whilst previous studies and The Department for Education have used the ‘good level of development’ (GLD) measure, this is a binary outcome and reduces all goals into one composite measure. An alternative to the GLD is to instead assign numerical scores to each category in the EYFSP (e.g., zero for emerging, one for expected, and two for exceeding), and sum these scores into a ‘total score’ composite (ranging between 0–34).

For each child, every goal met (or exceeded) will be assigned a one, and each goal scored as ‘emerging’ will be assigned a zero. The outcomes will be summed in the following ways:

For the primary outcome, we will examine only the most relevant ELG’s to child social and emotional development. These are the ‘communication and language’ and ‘personal, social, and emotional’ ELGs, with total 5 goals (see Table 2). The binary responses for each of these 5 goals will be summed to generate a summary score between 0 and 5.For the secondary outcome (child early years development), the binary responses for each of the 17 ELGs will be used to generate a summary score, where a total score between 0 and 17 will indicate how many of all the ELGs were assigned a score of ‘expected’.

**Table 2 pone.0291557.t002:** Overview of the covariates (matching variables, effect moderators, and covariates) to be included in model.

Covariates (measurement tool if relevant)	Measurement	References providing justification

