### Design

This effectiveness evaluation will use a quasi-experimental design. A quasi-experimental design lacks random assignment and uses self-selection (by which participants choose treatment or a lack of treatment for themselves) [26]. The analyses will use propensity score matching, where multiple control cases will be matched to intervention cases (see statistical methods for further details).

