**Matching variables for propensity score**		
Prenatal attachment (Prenatal Attachment Inventory)	Continuous	[10, 11, 41]
Prenatal Depression (PHQ-9)	Continuous	[10, 11, 41, 42]
Prenatal Anxiety (GAD-7)	Continuous	As above
Ethnicity	Categorical	[10, 11, 30, 41, 43]
Socioeconomic position (financial security)	Continuous	[30, 42, 44–46]
Speaks English	Binary	[30, 46]
Immigration status (proportion of life spent in UK)	Continuous	[30, 47, 48]
Length of time in COVID lockdown	Continuous	[49]

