### Statistical methods

A detailed statistical analysis plan will be preregistered on the Open Science Framework (OSF), this section is provided as a summary. Our analyses will use the propensity score matching method, which estimates the probability of a subject to receive a treatment conditional on the set of covariates. Matching patients with a similar estimated propensity score will create approximate balance for baseline characteristics [36]. The propensity score method will use one-to-*many* matching, by matching individual treatment cases to multiple control cases [37]. After matched groups have been created, ordinal logistic regression analyses will be run using group assignment as the independent variable, and the primary and secondary outcomes as the dependent variables.

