### Variables

The Directed Acyclic Graph (DAG) in Fig 2 identifies the confounding variables that will be used as matching variables in the propensity score [38, 39]. We will match on the 7 characteristics on the left-hand side of the graph (prenatal attachment, prenatal depression, prenatal anxiety, ethnicity, socioeconomic status, language status, and immigration status) to estimate the effect of treatment (IY-T) on the primary outcome (child social and emotional development).

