**Fig 2 pone.0291557.g002:**
[figure not shown]
Directed Acyclic Graph of associations between confounders, covariates, moderators, treatment exposure, and outcome. Notes: 1. SES = socioeconomic status. 2. The secondary outcome (children’s early years school skills) is not depicted here.

The justification for the selection of these variables is given in Table 2 below. Variables which affect program participation but not the outcomes should not be used in propensity score matching, as this increases the error in the estimated values [40]. Matching variables were therefore selected if they were thought to have an association with both uptake of treatment, and with the outcomes (child early years development), and there was evidence to suggest this was the case. See Table 2 for a summary of the evidence for using a matching variable, and the tested moderators of the effect. We have proposed that we will test the effects of four moderators: child age, programme delivery mode, family socioeconomic status, and ethnicity, however, this will only be possible if a sufficient sample size is reached.

All variables are obtained from the BiBBS baseline questionnaire, which takes place before the child is born (see https://borninbradford.github.io/datadict/bibbs/ for details).

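### Reception teachers rate the outcome, but the stated analysis ignores school: standard errors can be too small if enrolment varies by school, and the odds ratio biased only if enrolment also tracks school rating or teaching

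*Protocol article*

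**What the plan says.** All references are to the protocol article.

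- **Outcome.** "The EYFSP is completed by teachers for children when they reach age five, at the end of their last term in reception". Each early learning goal is scored as met or not met. The primary score sums five goals and the secondary score sums all 17.
- **Design.** Assignment is not random: "A quasi-experimental design lacks random assignment and uses self-selection".
- **Intervention.** On recruitment: "IY-T receive most of their enrolled participants through their own engagement with the community directly, and also through engaging with schools and nurseries".
- **Variables.** "We will match on the 7 characteristics on the left-hand side of the graph". These are prenatal attachment, depression and anxiety, ethnicity, socioeconomic status, language and immigration status. Table 2 lists the same seven and adds an eighth, "Length of time in COVID lockdown". On their source: "All variables are obtained from the BiBBS baseline questionnaire, which takes place before the child is born".
- **Statistical methods and Software.** After matching, "ordinal logistic regression analyses will be run using group assignment as the independent variable", fitted in Stata with ologit. A detailed analysis plan is to be preregistered, and the section describes itself as a summary.

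School, teacher and nursery appear in none of the matching list, the moderators, the outcome model, the sample size section, the robustness tests or the limitations.

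**The concern.** The only measurement of outcome is a judgement by school staff. Children in the same school share whoever makes that judgement, and they share a year of teaching before it is made. Two consequences follow for a model that treats children as independent.

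First, if the share of children whose parents enrolled differs from school to school, the between-school variation does not cancel between the arms. The reported standard error is then too small, even if enrolment has nothing to do with how high a school rates.

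Second, if enrolment is also related to a school's rating level or teaching quality, the school difference enters the odds ratio as if it were a programme effect. The matching variables may act as partial proxies for a school's intake, but they do not measure how strictly its teachers rate.

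The outcome is several years away (final analyses are planned after August 2028), and the Data management section says data are anonymised before researchers receive them. A school code that is not requested for the extract may be hard to add later.

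**Working it through.** **1. The plan's own figure.** The Sample size section gives 1336 (334 + 1002) for an odds ratio of 1.5, a 1:3 ratio and 80% power. It states neither alpha nor the category probabilities. Assuming a two-sided alpha of 0.05, the Whitehead proportional-odds formula is

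N = 3(A+1)²(z₀.₉₇₅ + z₀.₈₀)² / [A (ln OR)² (1 − Σp̄³)], with A = 3 and OR = 1.5,

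which gives N = 763.9 / (1 − Σp̄³). N = 1336 requires Σp̄³ = 0.428, or about 74% of controls at the top score of 5. That is plausible. The figure is therefore consistent with an individual-level calculation without a clustering term, but it cannot be confirmed.

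**2. School effect on the standard error.** The article gives no ICC, number of schools or enrolment share by school, so these are assumptions:

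- 45 schools and N = 1336 (about 30 children per school), with no programme effect
- 25% enrolled on average
- six outcome categories, with 73% at the top
- school effect normal on the log-odds scale, SD = √[ICC/(1 − ICC) × π²/3]
- log odds of enrolment varying between schools with SD 0, 0.5 or 1.0, **independent** of the school effect

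An SD of 1.0 means that a school one SD below average has about 11% enrolled and one SD above about 48%. For an SD of 0.5 the figures are about 17% and 35%.

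The school-blind test is the rank-sum (proportional-odds score) test; the comparison is a school-stratified van Elteren test. There were 1500 replicates per cell, so the Monte Carlo standard error is about 0.6 points at 5% and 0.8 points at 10%. Type I error (%):

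| ICC | School SD | Blind, enrolment SD 0 | Blind, SD 0.5 | Blind, SD 1.0 | Stratified, SD 1.0 |
|---|---|---|---|---|---|
| 0 | 0 | 4.7 | 4.9 | 4.4 | 4.0 |
| 0.05 | 0.416 | 4.9 | 4.7 | 7.3 | 5.1 |
| 0.10 | 0.605 | 4.6 | 6.3 | 8.5 | 5.9 |
| 0.15 | 0.762 | 4.9 | 5.3 | 10.0 | 4.7 |

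Inflation is clear only when enrolment differs strongly between schools. Converted to standard errors: a true error rate of 7.3%, 8.5% or 10.0% means that the nominal 1.96 cut-off acts like 1.79, 1.72 or 1.645. The standard error is then too small by a factor of 1.96/1.79 = 1.09, 1.96/1.72 = 1.14 or 1.96/1.645 = 1.19. Honest intervals would be about 9% to 19% wider.

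**3. School effect on the estimate.** To a first approximation, spurious log OR = (between-school SD) × (difference in mean school effect between the arms, in SD units). The article gives neither factor. For illustration only, 0.3 × 0.25 = 0.075 (OR 1.08) and 0.7 × 0.5 = 0.35 (OR 1.42). If the second factor is zero, there is no bias at any SD.

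**The case against.** **The analysis plan may deal with this.** The methods section is declared a summary, clustered errors are often left to the analysis plan, and naming ologit does not exclude a cluster option. Nor does the article say that group is the only predictor, and the Table 2 caption mentions covariates in the model. This is fair, and it is why the point is not that something is missing. However, the article does name the matching variables, the independent variable and the command. Taken as stated, that method treats children as independent, and no covariate listed anywhere is school.

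**The link between school and enrolment is weak or unknown.** This stands in large part. Most enrolment is through direct community work, with schools and nurseries as an additional route. The article does not say that only certain schools were engaged. Parents enrol two to four years before the rating, and nothing says that the school or nursery engaged then is the one that later rates the child. Both arms are cohort members recruited from the same three areas, which limits how far their schools can diverge.

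**Adjusting for school is itself contestable.** This also stands. Reception school is fixed after enrolment, so conditioning on it could remove part of an effect or introduce bias. A school-conditional odds ratio is also a different quantity from the one used for power. These are reasons not to replace the primary estimate with a within-school one.

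**Conclusion.** The point holds in a limited form. The outcome is rated within schools, and the stated analysis takes no account of school. If enrolment varies strongly between schools, the nominal 5% test has a true error of about 7% to 10%, under assumed ICCs of 0.05 to 0.15, 45 schools and an enrolment SD of 1.0 on the log-odds scale. With an SD of 0.5 it was 4.7% to 6.3%, and with none it stayed near 5%. Bias in the odds ratio needs the further condition that enrolment tracks school rating level or teaching quality.

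Two stronger readings are not supported:

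- A reader might infer that school differences will produce a false odds ratio close to the target of 1.5. The illustrative 1.08 to 1.42 rests on two assumed factors, and nothing in the article shows that intervention children are concentrated in higher- or lower-rating schools. The direction is equally unknown.
- A reader might apply the usual design effect, 1 + (m − 1) × ICC, and conclude that 1336 is far too few. That formula is for treatment assigned by whole school. Here treatment varies within schools, so it overstates the loss.

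**What to change.** - Request a pseudonymised school identifier from the linked education record in the analysis extract, and say so in the data specification.
- Keep the planned primary ordinal model and its estimate, but allow for school clustering in its standard errors (for example ologit with a school-clustered variance). Matched sets may cross schools, so the variance method has to handle both. The simulation above checked a stratified test, not this variance, so its behaviour should be verified once the number of schools is known.
- Pre-specify a sensitivity analysis of the within-school contrast: a school-stratified or school fixed-effect ordinal model among schools holding both groups. Show it beside the primary result.
- Tabulate the number of schools and the children per school by arm. This shows directly whether enrolment varies by school and whether the issue matters in these data.

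The cost is one extra field, a few lines in the analysis plan and somewhat wider intervals. Schools with only one group, or very few children, add little to the within-school contrast. Because school is fixed after enrolment, that contrast is supportive evidence and does not replace the primary estimate.

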**Moderators**		
Child age	Continuous	N/A
Programme delivery mode (face to versus or virtual)	Binary	N/A
Socioeconomic position (financial security)	Continuous	N/A
Ethnicity	Categorical	N/A

Participants who entered reception prior to or during September 2020 will be assessed according to the old version (though this is anticipated to be a small number of participants), and participants in IY-T who enter reception after or during September 2021 will be assessed according to the new version. The measures will be made comparable by collapsing all participants who met or exceeded goals to be assigned a one, and each goal scored as emerging will be assigned a zero.

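### The primary score is fixed at five goals (0 to 5), but Table 1 marks six primary goals for the old profile version, and the stated harmonisation rule does not close the gap

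*Protocol article*

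**What the plan says.** All of this stands in the protocol article, section on the outcome (early years foundation stage profiles).

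- **Definition.** The primary outcome uses the communication and language goals and the personal, social and emotional goals, five in total: "The binary responses for each of these 5 goals will be summed to generate a summary score between 0 and 5". The text points to Table 2 for these goals, but Table 2 lists covariates; the goals are in Table 1.
- **Table 1, note 2.** The bolded goals "are the goals used for the primary outcome". Bold type is used in both version columns.
- **Table 1, old version.** Bolded: "1. Listening and attention 2. Understanding 3. Speaking" and "6. Self-confidence and self-awareness 7. Managing feeling and behaviour 8. Making relationships".
- **Table 1, new version.** Bolded: "1. Listening, attention and understanding 2. Speaking" and "5. Self-regulation 6. Managing self 7. Building relationships".
- **Harmonisation rule (paragraph after Table 2).** Children who entered reception up to and including September 2020 are assessed on the old version and are expected to be few. For them, "The measures will be made comparable by collapsing all participants who met or exceeded goals to be assigned a one", with emerging goals set to zero.

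The sample size section says the score will be analysed with a proportional odds model.

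**The concern.** The definition, the table and the harmonisation rule cannot all be applied to an old-version child. Listening and attention, and understanding, are two goals in the old version and one in the new. Recoding exceeded to one removes the difference in response levels (three against two) but leaves six items against five.

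Two things are at stake. First, the primary score is undefined for a group of children the protocol says it will include, so the mapping could be chosen after outcomes are known. Second, if an analyst simply adds up the bolded goals, old-version children can reach a category that no new-version child can reach. Profile version would then move a child's ordinal category for reasons unrelated to the programme.

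**Working it through.** **1. Goal count (Table 1).**

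| Area | Old version | New version |
|---|---|---|
| Communication and language | 3 (goals 1, 2, 3) | 2 (goals 1, 2) |
| Personal, social and emotional | 3 (goals 6, 7, 8) | 3 (goals 5, 6, 7) |
| Total primary goals | 6 | 5 |
| Range of the sum of binary goals | 0-6 | 0-5 |

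The stated range fits the new version only. All areas together give 17 goals in both versions, so the secondary score has no count mismatch.

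**2. Is the stated sample size affected?** The plan gives 1336 (334 + 1002) for 80% power, odds ratio 1.5 and ratio 1:3. The category probabilities and the significance level are not stated, so the figure cannot be reproduced exactly. The Whitehead formula with r = 3 and an assumed two-sided 5% level is

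N = 3(r+1)²(1.960 + 0.842)² / [r (ln 1.5)² (1 − Σp³)] = 763.9 / (1 − Σp³).

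Setting N = 1336 gives Σp³ = 0.428. With six categories and the remainder spread evenly, that is a top-category share of about 0.75, so the figure is attainable. Moving from six to seven categories changes N by at most 2 for top-category shares of 0.5 to 0.8 (0.50: 879 against 877; 0.75: 1323 against 1323). The sample size is not the problem.

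**3. What literal summing would do to the odds ratio.** This is a population-level proportional odds fit with a 1:3 ratio. Old-version children are left on 0-6 and new-version children on 0-5. The assumptions, none of them given in the protocol, are the same top-category share in both versions (0.60 or 0.75), the rest spread evenly, and the old-version shares shown.

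| Old-version share, control / intervention | True OR | Fitted OR, top share 0.60 | Fitted OR, top share 0.75 |
|---|---|---|---|
| 5% / 5% | 1.0 | 1.00 | 1.00 |
| 5% / 5% | 1.5 | 1.46 | 1.42 |
| 5.9% / 2.8% | 1.0 | 0.95 | 0.92 |
| 2.8% / 5.9% | 1.0 | 1.05 | 1.10 |

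With a top share of 0.75 and a true odds ratio of 1.5, equal shares of 2% and 10% give 1.46 and 1.37.

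**4. Where 5.9% and 2.8% come from.** Assume even births from April 2016 (the earliest due date in the pilot data section) to April 2023 (the last child to reach 12 months by the end of delivery), and September to August school years. Old-version children are then those born April to August 2016: 5 of 85 birth months = 5.9% of potential controls. Delivery began in September 2018, so these children had 7, 8, 9, 10 and 11 eligible months left, 45 in all. The total over all 85 birth months is 1611 eligible months, and 45/1611 = 2.8%. That would be their share of the intervention group if uptake were even per eligible month.

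**The case against.** A reader might infer that old-version children are scored 0-6 and that the treatment odds ratio is therefore biased. The documents do not support that.

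- **No 0-6 score is stated.** The only range given is 0 to 5, for every child. What is shown is an undefined derivation for a subgroup, not a declared second scale.
- **Bias does not follow automatically.** With equal shares in both groups there is none under no effect, only attenuation of a real effect. With the imbalance reversed, the error changes sign.
- **The imbalance is not established.** The 5.9% describes the eligible pool, whereas the analysis uses matched controls. Even births and even uptake are assumptions. Table 2 lists time in COVID lockdown as a matching variable, which may partly track birth cohort.
- **The group may be very small.** The protocol expects few old-version children, and the limitations section says profile collection was paused during the pandemic. The pause is not dated, but the earliest cohort could be affected. If only 50% of old-version children had records, the 5.9% against 2.8% scenario would give a null odds ratio of 0.955-0.976; at 10% it would give 0.990-0.995.
- **Choices such as exact matching on version** belong to the analysis plan that the protocol says will be preregistered.

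These points stand, and they limit the size of the problem. They do not remove the inconsistency: the article itself states the goal count, the range and the comparability claim, and they conflict. Lockdown time is also not a dependable safeguard, because the section on variables lists seven matching characteristics and omits it.

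**Conclusion.** The inconsistency is certain and can be seen by counting: six bolded goals against a five-goal, 0 to 5 score, with a harmonisation rule that addresses response levels only. The stated range and the comparability claim do not hold for children entering reception by September 2020.

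The effect on the result is possible but not established in size or direction. It requires that the bolded goals be summed literally. The illustrative figures (a true 1.5 read as about 1.42-1.46 with 5% in each group; a null read as about 0.92-0.95 at 5.9% against 2.8%) rest on assumed score distributions and assumed shares. The protocol gives neither the number of old-version children nor their split between groups. The sample size and the secondary outcome's goal count are unaffected. The point deserves correction because it concerns the definition of the primary outcome and is cheap to settle in advance.

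**What to change.** Before outcome data are analysed:

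1. State one rule that puts both versions on 0 to 5. For example, count old goals 1 and 2 as a single goal, met only if both are met. Alternatively, restrict the primary analysis to new-version children.
2. Add a sensitivity analysis that excludes old-version children, or adjust for or stratify by profile version. This is useful even with a common range, because the personal, social and emotional goals also carry different titles in the two versions.
3. Correct the cross-reference for the primary goals from Table 2 to Table 1.

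The cost is one derivation rule and one extra analysis, with no new data. A few old-version children may be lost if the analysis is restricted or stratified. Other mappings, such as the proportion of goals met, would also resolve the contradiction; what matters is that one is fixed in advance.
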